#### Syndemic constructs

Syndemic constructs include social adversity (socioeconomic adversity and traumatic events) and mental, physical and oral multimorbidity.

Socioeconomic adversity will be measured by socioeconomic position (SEP) indicators at individual, household and neighbourhood (area) levels: education, employment, income and deprivation. Education is measured at an individual level and will be categorised into high (college/vocational training or above) and low (A levels, AS levels, or equivalent; O levels, GCSEs, or equivalent; CSEs or equivalent; NVQ, HND, HNC, or equivalent; other professional qualifications; and “none of the above”). Employment status is measured at an individual level and will be grouped into: employed (including those in paid employment or self-employed, or doing unpaid or voluntary work) and unemployed (including being retired, full or part time students, unemployed, looking after home and/or family, or unable to work because of sickness or disability). Income is measured by the annual total household income before taxes are deducted. It will be categorised into 0 (>£100,000), 1 (£52,000-£100,000), 3 (£31,000-£51,999), 4 (£18,000-£30,999), and 5 (<£18,000). Area deprivation is measured by Townsend deprivation index quintiles. The two quintiles with the highest area deprivation scores will be scored 1 (indicating high levels of area deprivation), and the rest of quintiles will be scored 0 (indicating low levels of area deprivation).

Traumatic events will include felt hated by family member as a child, did not feel loved as a child, physically abused by family as a child, sexually molested as a child, no one to take to doctor when needed as a child, victim of physically violent crime, victim of sexual assault, witnessed sudden violent death, belittlement by partner or ex-partner as an adult, physical violence by partner or ex-partner as an adult, sexual interference by partner or ex-partner without consent as an adult, and been involved in combat or exposed to war-zone.

Mental multimorbidity will include mood disorders and severe mental illness (ICD-10 codes: F20-F29; F31; F33-34).

Physical multimorbidity will be measured using Ronaldson et al. approach that comprises a total of 36 long term physical health conditions (**Supplementary Table 1**) (22).

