#### Syndemic constructs

Syndemic constructs include social adversity (socioeconomic adversity) and mental, physical and oral multimorbidity. No data is available in NHANES on traumatic events.

Socioeconomic adversity will be measured by SEP indicators at individual and household levels: education, employment, occupation, income and health insurance. Education is measured at an individual level and will be categorised into high (college or above) and low (high school diploma or below). Employment status is measured at an individual level and will be grouped into: employed (working at a job or business or with a job or business but not at work) and unemployed (looking for work or not working at a job or business). Occupation is measured using socioeconomic index, which is based on the employees’ earnings, education level and prestige. It will be categorised based on the median into upper and lower level and unemployment. The lower level will include retirees and students. Income is measured by family income ratio to the federal poverty line (<100%, 100%-199%, 200%-399%, >400%). Health insurance will be categorised into private health insurance (including any private health insurance, Medi-Gap or single-service plan), public health insurance only (including Medicare, Medicaid, State Children’s Healthcare Plan, military healthcare, Indian Health Service, State Sponsored Health Plan or other government programme) and no health insurance. No data is available in NHANES on area deprivation.

Mental multimorbidity will include depression (“moderately-severe” or “severe” depressive symptoms versus “moderate”, “mild” or “no” depressive symptoms; as measured by the PHQ-9) and severe mental illness (as measured by medicines prescribed in the past month for severe mental illness).

Physical multimorbidity will be measured using Ronaldson et al. approach (**Supplementary Table 1**) (28). However, not all the 36 long term physical health conditions are reported in NHANES (such as bronchiectasis, psoriasis and polycystic ovarian syndrome). Only those that are available in NHANES will be used to indicate the physical multimorbidity construct.

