#### Mediators

Mediators are health behaviours and lifestyle, and C reactive protein.

Health behaviours and lifestyle variables will include obesity (BMI>=30), alcohol intake (healthy versus unhealthy level; the former is defined as daily consumption of one drink or fewer for women and two drinks or fewer for men, according to the dietary guidelines in the US - one drink contains 14g of ethanol in the US), smoking (healthy versus unhealthy levels; the former is defined as never smoked or smoking fewer than 100 cigarettes in life), physical activity (healthy versus unhealthy; the former is defined as 150 minutes of moderate-intensity physical activity weekly or 75 minutes of high-intensity physical activity weekly), poor appetite or overeating (Yes versus No), diet quality (healthy versus unhealthy; the former is defined as the health eating index in the top two fifths of distribution), trouble falling/staying asleep or sleeping too much (Yes versus No), ever addicted to any substance or behaviour (Yes versus No), number of sexual partners in the past year, inconsistent condom use (“never” versus “occasionally” or “always”), toothbrushing (twice daily versus less than twice daily), dental flossing (once daily versus less than once daily) and dentist visiting (once every two years or more versus less than once every two years).

The level of CRP is used as a marker of bodily inflammation and presented in mg/L.

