#### Statistical analysis

Descriptive statistics will be used to summarise participants characteristics. For NHANES and RELACHS data, survey analysis procedures will be used to account for the sample weights, stratification and clustering of the complex sampling design to ensure representative estimates.

To answer the research questions on the presence of syndemic relationships, a structural equation modelling (SEM) technique will be utilised to conceptualise syndemic constructs and model complex relationships between directly observed and indirectly observed (latent) variables. The SEM technique has gained increasing popularity in syndemic research (30, 31). To use this technique, the following steps will be undertaken:

In step one, exploratory and confirmatory factor analyses will be used to identify the clustering nature and reduce the number of indicators (observed variables) under each theoretical construct. In step two, a SEM to predict premature mortality and all-cause hospitalisation, controlling for age, sex and ethnicity, will be run. Analysis will include identifying whether the indicators chosen to measure the latent constructs are acceptable. confirmatory factor analysis will be used to provide information on how indicator items measure underlying (latent) constructs. In step three of the analysis, SEM will be used to examine the direct and indirect relationships between the constructs. The goodness of fit (GoF) of the SEM model to the data will be assessed considering the indices of Comparative Fit Index (CFI) and Tucker-Lewis Index (TLI; where values >.90 indicate a good fit), root mean square error of approximation (RMSEA), and Standardised Root Mean Square Residual (SRMR; where value <.05 indicate a good fit). In step four, the synergistic (multiplicative) interactions between different latent constructs and measured variables will be tested using two-step estimation procedures (32).

To answer the question on whether syndemic relationships vary by age, sex and ethnicity, stratified analyses by age, sex and ethnicity will be performed.

Full Information Maximum Likelihood technique will be used as a pragmatic approach for data missing estimation for SEMs. This approach produces unbiased parameter estimates and standards errors (33). For UK BioBank and RELACHS datasets, stability of exposure data over time will be checked by calculating the intraclass correlation coefficients between baseline and follow up data.

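### In NHANES, two behavioural mediators carry the wording of PHQ-9 symptom items although the PHQ-9 also defines depression, and the condom-use split contradicts its label

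*Protocol article*

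**What the plan says.** Under NHANES methods, Syndemic constructs, mental multimorbidity has two indicators. One is depression, split at moderately severe or worse and taken from "depressive symptoms; as measured by the PHQ-9) and severe mental illness". The other is severe mental illness, judged from prescribed medicines.

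Under NHANES methods, Mediators, the article states "Mediators are health behaviours and lifestyle, and C reactive protein". It then lists 13 behaviour and lifestyle variables. Three matter here:

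- sleep: "trouble falling/staying asleep or sleeping too much (Yes versus No";
- appetite: "poor appetite or overeating (Yes versus No";
- condom use: "inconsistent condom use (“never” versus “occasionally” or “always".

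Under Statistical analysis, step one uses factor analysis to cut down the indicators within each theoretical construct. In step three, "SEM will be used to examine the direct and indirect relationships between the constructs".

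The article does not say that the sleep and appetite items are removed from the PHQ-9 score, drawn from another source, or given correlated errors with the depression indicator.

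**The concern.** A mediator has to be measured separately from the construct it is linked to. Otherwise a path between them partly reflects an instrument correlated with itself. Two of the listed mediators read as symptoms that the depression questionnaire already scores. The phrasing itself points that way: each one joins opposites (eating too little with eating too much, sleeping too little with sleeping too much). That is how a depressive symptom is screened, not how a behaviour is graded. Diet quality is also listed as its own mediator.

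At stake is how the direct and indirect paths of step three are read. A reader could not separate a behavioural pathway from shared item content.

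The condom variable raises a simpler problem. Its label and its categories disagree, so it cannot measure what it is named for.

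**Working it through.** **Overlap: inputs from the article.** Depression comes from the PHQ-9, dichotomised (NHANES, Syndemic constructs). Sleep and appetite are separate yes/no mediators (NHANES, Mediators). Direct and indirect paths are estimated between constructs (Statistical analysis). The article gives no figure for this point, so there is none to reproduce.

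**Assumptions, not in the article.** The PHQ-9 has nine items scored 0 to 3, two of which are the sleep and appetite items, and moderately severe means a total of at least 15.

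**Step 1: weight of the shared items.**

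- Share of items: 2/9 = 22%.
- Share of the maximum score: (2 × 3)/(9 × 3) = 6/27 = 22%.
- Maximum contribution relative to the cut: 6/15 = 40%.

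**Step 2: what overlap does to the association.** An illustrative probit factor model was run with 1,000,000 subjects per scenario. Assumed item probabilities for scores 0, 1, 2 and 3 were 0.70, 0.18, 0.07 and 0.05. The other seven items correlate 0.5 or 0.6 with each other. Sleep and appetite correlate with those seven at the value shown. The mediator is positive when the sleep item scores above 0. Depression is defined in two ways: all nine items at 15 or more, or the other seven items at the rescaled cut 15 × 21/27 = 11.7, which means 12 or more.

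| Correlation among other seven | Correlation of sleep and appetite with them | Odds ratio, nine items | Odds ratio, seven items | Ratio |
|---|---|---|---|---|
| 0.6 | 0 | 1.53 | 1.00 | 1.53 |
| 0.5 | 0 | 1.65 | 1.00 | 1.65 |
| 0.6 | 0.3 | 5.72 | 3.50 | 1.63 |
| 0.5 | 0.5 | 30.62 | 14.65 | 2.09 |
| 0.6 | 0.6 | 46.27 | 23.56 | 1.96 |

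The first two rows isolate the artefact: sleep is unrelated to the other items, yet scoring it within depression produces an odds ratio of about 1.5 to 1.7. In the other rows the odds ratio is again higher with overlap, but most of the association is genuine under the assumed model. A seven-item score is also a somewhat weaker measure of the same factor, so not all of the last column need be overlap.

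**Step 3: does the plan already deal with it?** Step one of the analysis reduces indicators under each construct. It is not stated to search for content shared between a construct and a mediator.

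**Condom use: label against coding.** There are three response categories. A variable for inconsistent use has to separate *always* from *occasionally*. The written split puts *never* on one side and *occasionally* with *always* on the other. It therefore contrasts no use with any use. No calculation is needed.

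**The case against.** The strongest objection is that the article names the PHQ-9 but lists no items, scoring or cut, and gives no source for the two mediators. That the answers are the same is an inference from wording. This stands as a limit, and it is why the point is conditional. The match covers both phrases, and nothing in the article points to another source.

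A reader might infer that UK BioBank has the same fault, because its Mediators section lists the same two phrases. The article does not support that: "Mental multimorbidity will include mood disorders and severe mental illness (ICD-10 codes: F20-F29; F31; F33-34". No answer is scored twice there. Whether a symptom may mediate the effect of a diagnosed disorder is a matter of modelling judgement, not an error.

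A reader might also take the strong association between these items and depression as the size of the fault. It is not. With an assumed correlation of 0.5 to 0.6 the odds ratio is still 15 to 24 after both items are removed from the score, against 31 to 46 with them.

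Nor do the documents settle which path is affected. The Introduction describes behaviour as a route from social adversity to disease, and Figure 1 is not shown. It would go too far to say that the behavioural share of a mental-health effect on the outcome is inflated by some amount. Overlap matters in either direction of the path, but no indirect effect has been estimated here.

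It can also be said that the variables are candidates and that factor analysis may drop some. That is possible, but it is not a stated safeguard against overlap.

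On condom use, never versus any use is a workable contrast, so renaming would cure the contradiction. That is fair, and the fix allows for it.

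**Conclusion.** The point holds for NHANES only. If the sleep and appetite mediators are PHQ-9 items, as their wording indicates, any path between the mental construct and these mediators is partly built in by shared scoring. Under the assumed nine-item, 0 to 3 scoring with a cut of 15, overlap alone yields an odds ratio of about 1.5 to 1.7 in place of 1.0. The resulting bias in the indirect effect is unknown. It depends on the final model, in which PHQ-9 depression is one of two mental indicators and these are two of 13 listed behaviour variables.

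The condom-use contradiction is certain from the text alone but minor: one variable, in one of three datasets, that pools inconsistent with consistent users.

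Both should be put right before the NHANES models are fitted. Neither undermines the project as a whole.

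**What to change.** **Sleep and appetite, NHANES models only.** State the source of the two variables. If it is the PHQ-9, do one of the following:

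- drop both as mediators;
- take sleep and appetite from a measure outside the PHQ-9, if the chosen cycles hold one;
- score depression without the two items in the models that include them as mediators, and state the adapted cut.

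The first option loses up to two mediators. Diet quality remains on the list, but no other sleep variable does, and the NHANES list moves further from the UK BioBank list that the article tries to match. The third gives a non-standard depression score.

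**Condom use.** Recode as *never* or *occasionally* versus *always*. If never versus any use is what is wanted, keep the split and rename the variable.

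All of this is recoding of data already held.

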#### Covariates

Covariates are demographic variables: age, sex and ethnicity.

### RELACHS research questions

RELACHS database will be used to answer the following research questions:

Are there syndemic relationships between social adversity and mental, physical and oral multimorbidity impacting self-reported general health?Do these syndemic relationships vary by age, sex and ethnicity?

### RELACHS methods

#### Design and study population

RELACHS is a 3-phase longitudinal school-based survey of a representative sample of a very ethnically and culturally diverse young people population residing in East London. Schools in the London boroughs of Hackney, Tower Hamlets and Newham were randomly selected and balanced to ensure representation of single and mixed sex schools. Children from Year 7 and Year 9 were recruited at baseline (time 1). Data from phase 1 (for syndemic constructs, mediators and covariates) and phase 3 (for the syndemic outcome) will be used. It is worth noting that oral health related data were only collected in phase 3.

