Social adversity precipitates and exacerbates clusters of mental and physical diseases and conditions (**Figure 1**). For example, socioeconomic adversity (such as having low income, being unemployed or living in a deprived area) and traumatic events (such as adverse childhood experiences, being a victim of physically violent crime or sexual assault) are linked to compounded mental and physical conditions via systemic inflammation and behavioural pathways (10, 11). The situation can be further compounded by barriers to accessing healthcare (12). For instance, people with severe mental illness may experience under-recognition and under-treatment of physical conditions such as cardiovascular disease (12–14). In turn, these clustering mental and physical conditions reinforce each other through bidirectional interactions, that are also shaped by the social and contextual factors, leading to multiplicated mortality and morbidity burdens (8).

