#### Syndemic outcome

The syndemic outcome is self-reported health at phase 3 (very good, good versus fair, bad, very bad).

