#### Mediators

Mediators are health behaviours and lifestyle. No data is available in RELACHS on C reactive protein or other inflammatory markers.

Health behaviours and lifestyle variables will include being overweight or obese (having BMI above the 85th percentile and 95th percentile, respectively); alcohol consumption (never tried versus tried alcohol or consumed alcohol in the past week), smoking (never smoked versus ever tried or regular smoker), drug use (never tried versus tried drugs: cannabis, glue/solvents/gas, ecstasy, crack, heroin, amphetamines, LSD, cocaine and/or khat), physical activity (active versus inactive, exercising more or less than twice a week for an hour), diet as measured by the frequency of consumption of breakfast, crisps/savoury snacks, sweets, biscuits, fried food and fizzy drinks (“never”, “hardly ever”, “1-2 days a week” versus “3-4 days a week” or “daily”) as well as daily consumed portions of fruits and vegetables (5 or more portions daily versus less than 5 portions daily or none); dieting behaviour as measured by ever dieted to lose weight (Yes versus No) as well as present attempts to diet to lose or gain weight (Yes versus No); and tooth brushing (twice daily versus less than twice daily).

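### In RELACHS the constructs and behavioural mediators both come from phase 1, so the construct-to-mediator leg of the planned indirect effects is cross-sectional

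*Protocol article*

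**What the plan says.** The RELACHS methods (Design and study population) describe the source: "RELACHS is a 3-phase longitudinal school-based survey". They then assign variables to waves: "Data from phase 1 (for syndemic constructs, mediators and covariates) and phase 3 (for the syndemic outcome) will be used". Phase 2 is not mentioned in the model. The one exception noted there is that "oral health related data were only collected in phase 3"; that is a separate difficulty and is not part of this point.

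The RELACHS outcome section confirms the end of the path: "The syndemic outcome is self-reported health at phase 3". The RELACHS Mediators section makes behaviour the only route that can be studied: "Mediators are health behaviours and lifestyle. No data is available in RELACHS on C reactive protein or other inflammatory markers".

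The Statistical analysis section, step three, plans the mediation: "SEM will be used to examine the direct and indirect relationships between the constructs". It describes no step that orders mediators in time. Its only other use of repeated RELACHS data is an intraclass correlation check on the stability of exposures, and it does not name the follow-up phase used for that.

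**The concern.** An indirect effect has two legs, construct to mediator and mediator to outcome. In RELACHS the second leg runs from phase 1 to phase 3. The first leg lies within one survey. Depression and mental health problems are recorded at the same time as smoking, alcohol, drug use, diet and activity, so the data cannot separate low mood leading to smoking from smoking leading to low mood, or either from a shared cause.

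The measures sharpen this. Several mediators ask whether something was ever tried (alcohol, smoking, drugs, dieting), while at least one response option of the bullying item refers to the current school term. A mediator may therefore predate the exposure whose effect it is supposed to carry.

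For one pathway the gap is complete. The Introduction says that socioeconomic adversity and traumatic events "are linked to compounded mental and physical conditions via systemic inflammation and behavioural pathways". In RELACHS the path from adversity through behaviour to mental or physical multimorbidity lies wholly within phase 1, so the survey waves order neither leg. At stake is whether associations present at phase 1 are reported as mediation.

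**Working it through.** The article gives no figure to reproduce here. The wave assignment is read from the text, and the size is illustrated with assumed standardised values that are not in the document.

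**Wave of each element (RELACHS methods).** Social, mental and physical constructs: phase 1. Behavioural mediators: phase 1. Self-reported health: phase 3.

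**Can model fit choose the direction?** Let X be a construct and M a behaviour, both at phase 1, and Y health at phase 3. Assume r_XY = 0.2 and r_MY = 0.3, and vary r_XM.

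- Coefficient of M on Y given X: b = (r_MY − r_XM·r_XY)/(1 − r_XM²)
- Coefficient of X on Y given M: c = (r_XY − r_XM·r_MY)/(1 − r_XM²)
- Indirect effect if X→M→Y: r_XM·b. Indirect effect if M→X→Y: r_XM·c

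At r_XM = 0.3: b = (0.3 − 0.06)/0.91 = 0.264 and c = (0.2 − 0.09)/0.91 = 0.121. The indirect effects are 0.3 × 0.264 = 0.079 and 0.3 × 0.121 = 0.036.

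| r_XM | X→M→Y | M→X→Y |
|---|---|---|
| 0.1 | 0.028 | 0.017 |
| 0.3 | 0.079 | 0.036 |
| 0.5 | 0.133 | 0.033 |

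In every row both models return r_XY = 0.20 and r_MY = 0.30 exactly, so CFI, TLI, RMSEA and SRMR cannot tell them apart. The two columns are also different quantities: if M causes X, the effect of X through M is zero, and 0.036 is the effect of behaviour through the construct.

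**What would a phase 2 mediator add?** Assume a phase 1 construct-behaviour correlation of 0.2, behaviour stability of 0.6 from phase 1 to phase 2, an effect of phase 2 behaviour on health of 0.2, and a direct construct effect of 0.1.

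1. Phase 1 model: the behaviour coefficient is 0.6 × 0.2 = 0.12, the indirect effect is 0.2 × 0.12 = 0.024, and the mediated share is 0.024/(0.024 + 0.100) = 19%.
2. Phase 2 mediator, unadjusted: the construct-to-mediator path is 0.2 × 0.6 = 0.12, and the indirect effect is 0.12 × 0.2 = 0.024.
3. Phase 2 mediator, adjusted for phase 1 behaviour: the construct-to-mediator path is 0.00.

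These three results are the same whether behaviour caused the construct (true mediated share 0%) or the construct caused behaviour before phase 1 (true share 19%). The adjusted path is non-zero only if the construct changes behaviour after phase 1. A non-zero adjusted path therefore supports an ordered effect, but a zero does not rule out mediation established earlier.

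**The case against.** A reader might infer that the RELACHS indirect effects have no time order at all. The text does not support that for paths ending in the declared outcome, because phase 1 behaviours precede phase 3 health. It is true only of paths that stay within phase 1.

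A reader might also infer that reverse causation threatens every construct equally. It does not. Free school meals, home and car ownership, parental employment and overcrowding are not plausibly caused by a pupil's smoking or diet, and the same holds for being looked after or a close family death. Some of those events may also predate the survey. Confounding remains there, but reverse causation is a minor issue.

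Nor does the Introduction concede the point. It calls the links among mental, physical and oral conditions bidirectional, not the links between conditions and behaviours.

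A further objection is that phase 2 may be no remedy. The article lists no items by wave, so the behaviours may not have been repeated. The planned stability check concerns exposures and might use phase 3. RELACHS also cannot safely be called the only database with an intermediate wave, since follow-up data are mentioned for UK BioBank too. Finally, as the working shows, adjusting for phase 1 behaviour can remove genuine mediation along with the artefact.

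All of this stands, and it limits the point and the remedy. It does not give the first leg a time order.

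**Conclusion.** The concern holds in a bounded form. For the social, mental and physical constructs in RELACHS, the construct-to-mediator leg is cross-sectional by an explicit choice of wave, and the planned fit indices cannot supply the missing direction. It matters chiefly for depression, mental health problems and bullying. It also matters for any path from adversity through behaviour to mental or physical multimorbidity, which lies wholly within phase 1.

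The size cannot be derived from the article. Under the assumed correlations, an indirect effect of 0.028 to 0.133 would be reported for the construct when the true value is zero if behaviour came first. The 19% share is likewise an illustration: the same figure is correct if the construct came first, so it shows ambiguity and not a known bias. The plan should be changed or its wording restricted before analysis; the phase 1 to phase 3 associations remain usable.

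**What to change.** 1. Establish which behaviour items were repeated at phase 2. That they were is an assumption here.
2. Where they were, fit the indirect-effect model with phase 2 mediators, once with and once without adjustment for their phase 1 values, and report both beside the phase 1 model.
3. State that the adjusted model captures only change in behaviour after phase 1 and may miss mediation already established by then.
4. Where phase 2 items are not available, report the phase 1 construct-behaviour paths as cross-sectional associations and do not call them mediation. Phase 2 mediators do not order a path that ends in phase 1 multimorbidity, so the same wording should apply to paths that lie wholly within phase 1.

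Cost: one additional model, fitted with and without the adjustment, and a change to the variable list; no new data collection, provided the items exist. Phase 2 non-response will add missing data. The planned full information maximum likelihood handles this only under missing at random, which is open to doubt if drop-out depends on the behaviours themselves. Step 4 needs no further data and can be adopted whatever phase 2 contains.
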